## Abstract

**Supplementary Information:**

The online version contains supplementary material available at 10.1186/s40359-025-03326-3.

## Background and rationale {9a,b}

Early childhood is a formative period, with the parent–child relationship playing a critical role in subsequent cognitive and social development (e.g., Landry et al. [18], Lugo-Gil & Tamis-LeMond [20]). When parents of young children experience elevated distress (e.g., depression, anxiety, and anger), it can disrupt the ability to form or maintain healthy, dyadic relationships. This puts children at risk for negative outcomes, including difficult temperaments, altered cognitive development, insecure attachment and socioemotional risks [10, 17, 19, 22, 23, 26, 32, 34, 37]. Furthermore, the Intergenerational Transmission of Stress model, which has been used extensively to assess child developmental trajectories (see Bowers & Yehuda [7], Hammen et al. [11]), posits that children exposed to elevated parental distress experience increased levels of stress themselves. This leads to an increased risk of experiencing their own mental health challenges, linked to both genetic and environmental influences [11]. The risks of negative child developmental outcomes are positively correlated with parental distress severity (e.g., Mensah & Kiernan [23], Shonkoff & Fisher [32]). Furthermore, interventions designed to improve parental mental health have also contributed to improvements in child functioning [9]. By ensuring Canadian parents receive adequate mental health supports, we can effectively disrupt the intergenerational transmission and adverse impact of mental health concerns within the family [27]. Despite the well documented impacts of untreated parental distress on child development [17, 22], Canadian families continue to face a multitude of barriers to accessing effective and timely mental health resources (e.g., long wait times, limited free, community or public health resources) [24]. These barriers to accessing parental mental health supports put Canadian children at greater risk for cognitive and socioemotional challenges. Lack of access to timely treatment can worsen the severity of symptoms among families, increasing their distress and challenges over time. Low-barrier interventions that provide timely support can help mitigate these effects and reduce the strain on existing healthcare services.

In response to the growing need for accessible family mental health support, an app-based program entitled BEAM (Building Emotional Awareness and Mental Health; thebeamprogram.com) was launched in 2020. Through several pilots and randomized controlled trials (See Joyce et al. [13], MacKinnon et al. [21], Xie et al. [38], Xie et al. [39]), the BEAM program has offered a combination of parenting and mental health supports including (1) expert-led videos and related activities (e.g., exercises to reinforce skills from videos) (2) online closed group forums (3) symptom monitoring and (4) trial specific online group telehealth sessions led by clinical psychologists or parent-peer coaching. The program has seen positive changes in parental mental health, including improvements in parent anxiety, anger, and sleep, as well as reduction of harsh and negative parent–child interactions [21]. To support families across Canada, we propose the translation of BEAM into LightBEAM, a Massive Online Open Intervention (MOOI) delivered through an app-based platform. By translating BEAM into a MOOI format, we hope to be able to reach and support more families nationwide as the current BEAM trials have been available to only select provinces and limited by clinician availability.

Massive Online Open Intervention (MOOIs) deliver open access, evidenced-based behavioral interventions online through websites or apps [25]. Participants have full autonomy to access these self-directed interventions, which increases intervention reach and scalability by negating the limitations associated with individualized services (e.g., number of available clinicians in each community; Kazdin [15], Muñoz et al. [25]). Furthermore, the MOOI design can address common barriers to accessing services (e.g., cost associated with individualized services; Muñoz et al. [25]). Despite the potential strengths of the MOOI design, a one-size fits all approach to online mental health supports may not be appropriate for all individuals and the lack of direct clinical contact and individualized services leaves room for risk factors to be missed. Given both the strengths and limitations surrounding the MOOI format, more research is needed to explore the success of such programs in the context of mental health service delivery.

In response to the need for more empirical evidence for Massive Online Open Intervention mental health interventions, we are translating BEAM, an evidenced-based parenting and mental health app intervention into LightBEAM, a MOOI app. Our aim is to create an accessible mental health support for Canadian families. While several different MOOI programs exist, many are designed to support broader self-management health behaviors (e.g., smoking cessation programs), with few specifically focused on the translation of mental health and parenting interventions. The potential use of LightBEAM has a broad reach, providing support to families in remote areas with limited in-person services, offering interim assistance while they await individualized care, and serving as a self-referral program. By supporting parent mental health, the LightBEAM program may help foster healthy child and family development, thereby disrupting the negative impact of parental distress on healthy child development.

### Objectives {10}

There are three main aims of the proposed study. The first aim is to assess the feasibility and acceptability of the LightBEAM program. Metrics to examine feasibility will include recruitment and retention rates, participant satisfaction, and an exploration of unmet needs. As a way to explore feasibility, we will utilize qualitative focus groups to examine ways in which the program can be improved to better support Canadian families. Aim two is to examine the efficacy of LightBEAM at improving family outcomes when compared to a waitlist control condition. Primary outcomes for parents include mental health, distress, and parenting quality. Secondary outcomes for children include child well-being and socioemotional development. Aim three is to identify groups associated with the greatest program engagement and improvements. This will promote equity and be used to inform future programming.

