11	Boundary setting to make space for everything else	Memory making with your kiddo
12	Staying well and moving forward	Recipe for wellness

#### Aim 2

All eligible participants must present with at least one elevated symptom of concern across parental anxiety (GAD-7), depression (PHQ-9), anger (PROMIS) and/or parenting stress (PSI). Based on which metric(s) participants screen in as being elevated, an individualized composite primary score will be created whereby we examine whether there is a statistically significant change in elevated symptoms of concern across assessment time points. To examine the efficacy of the LightBEAM program in improving parental outcomes, a multi-level model with random intercepts will be utilized to assess the effect of treatment over time based on conditions. An intent to treat approach will be followed such that all randomized participants are included in analysis, regardless of completion.

Specifically, we will examine pre-to-post-to follow up program changes in primary and secondary outcomes. Such analysis will allow us to examine the efficacy of the LightBEAM program compared to other community resources. Program engagement metrics (e.g., number of videos watched, see Table 4) will also be included as moderators to probe whether participant changes are due to program engagement. This dosage analysis will be an exploratory analysis.

**Table 4 Tab4:** Aim 1 feasibility and acceptability metrics

	Indicator	Benchmark	Rational
Recruitment Rate	Number of parents recruited per month	Approx. 50 parents	We want at least 50 parents in the forum to ensure maximum engagement
Retention Rate	% of parents with follow up data	> 70% of parents with follow up data	Average retention rate amongst previous MOOI’s is 70%
Forum Use	# of posts and comments made on the forum	> 50% of users engage at least once in the forum (i.e., through posting, responding or interacting with a message)	This is an exploratory outcome. Based on previous work that showed 57% engagement in the BEAM forum
Videos watched	% of videos watched at least 50% of the way through	Participation in > 50% of the LightBEAM Content	Utilizing same benchmark (e.g., 50%) used in previous BEAM pilot studies [13]
Symptom tracking	# of weekly surveys completed	Participation in > 50% of symptom tracking exercises	Based on benchmark used in previous BEAM pilot studies

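### The Objectives and the Aim 2 analysis define the primary outcome differently, and neither fixes which outcome or which wave decides efficacy

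*Protocol article*

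**What the plan says.** Objectives {10} sets Aim 2 as efficacy against a waitlist control and states "Primary outcomes for parents include mental health, distress, and parenting quality". These are domains; no instrument or time point is attached.

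Statistical methods {27a, b}, Aim 2, takes a different route. Participants screen in on one or more of GAD-7, PHQ-9, PROMIS Anger and PSI, and from the screened-in scale(s) "an individualized composite primary score will be created". The test attached to that score is whether there is a "statistically significant change in elevated symptoms of concern across assessment time points". The next sentence gives the model: "a multi-level model with random intercepts will be utilized to assess the effect of treatment over time based on conditions". The following paragraph returns to the plural: "we will examine pre-to-post-to follow up program changes in primary and secondary outcomes".

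Trial design {12}, Re-baselining questionnaires and Online orientation session say that the intervention arm's post-intervention questionnaires coincide with the waitlist arm's re-baselining questionnaires, after which the waitlist arm receives LightBEAM. Further questionnaires follow at six months.

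**The concern.** A reader of the Objectives would expect three parent domains to carry the efficacy claim, parenting quality among them. A reader of Aim 2 would expect one symptom score that leaves parenting quality out. The two can give different answers: the composite might show no arm difference while the Parenting Scale does, or the reverse. Nothing in the article says which result would then stand as the answer to Aim 2.

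The wave raises the same question, since a difference at post-intervention and a difference at six months do not mean the same thing once the waitlist has had the programme. In addition, participants enter because their symptoms are elevated, so improvement over time in both arms is plausible. A sentence that judges the primary score by change across time points invites that improvement to be read as benefit.

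Outcomes are self-reported, and the Blinding section states that participants, analysts and the principal investigator know the allocation. Where the deciding outcome is open under those conditions, it can be settled after results are seen.

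**Working it through.** **1. Do the two definitions agree?**

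- Objectives {10}: mental health, distress, parenting quality.
- Aim 2: the screened-in scale(s) among GAD-7, PHQ-9, PROMIS Anger and PSI.

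The Parenting Scale, the nearest instrument to parenting quality in Table 1, is not a screening measure and cannot enter the composite. PSI does not obviously fill the gap, because Exploratory Analyses {27d} lists parenting quality and parenting stress as separate factors. The definitions therefore differ in content, not only in level of detail.

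**2. Is the composite defined for everyone analysed?**

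Co-parents go through randomization (Participant identification, recruitment, and consent {20, 32a}), need not report distress (Eligibility criteria {14a}) and do not complete the screener (Participant timeline {18}). A score built from screened-in scales cannot be formed for them, yet Aim 2 says all randomized participants are analysed.

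**3. Which wave gives a comparison with untreated controls?**

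- Pre-intervention: neither arm has had LightBEAM.
- Post-intervention/re-baselining: the intervention arm has had it and the waitlist arm has not.
- Six-month follow-up: the waitlist arm has been given access.

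Only the second wave estimates LightBEAM against no LightBEAM. Aim 2 names all the waves and gives none priority.

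**4. What could the ambiguity cost in error rate?**

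The article states no alpha, power or error rate, so there is no figure to reproduce; the sample size of 200–500 rests on feasibility. The following are assumptions: two-sided 5% per test, k outcomes at one wave, success if any one is significant, and equal pairwise correlation ρ. The choice of k = 3 follows the three named domains. The choice of k = 5 counts PHQ-9, GAD-7, PROMIS Anger, PSI and the Parenting Scale, which is a mapping the article does not make.

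For independent outcomes:

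- Either direction: 1 − 0.95^k. For k = 3, 1 − 0.857 = 14.3%. For k = 5, 1 − 0.774 = 22.6%.
- In favour of LightBEAM only: 1 − 0.975^k. For k = 3, 1 − 0.927 = 7.3%. For k = 5, 1 − 0.881 = 11.9%.

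For ρ > 0, k equicorrelated normal test statistics were simulated (1,000,000 draws per setting, no true effect on any outcome).

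| k | ρ | either direction | in favour of LightBEAM |
|---|---|---|---|
| 3 | 0 | 14.3% | 7.3% |
| 3 | 0.5 | 12.5% | 6.3% |
| 3 | 0.8 | 9.9% | 5.0% |
| 5 | 0 | 22.6% | 11.9% |
| 5 | 0.5 | 18.3% | 9.2% |
| 5 | 0.8 | 12.7% | 6.4% |
| 1 | – | 5.0% | 2.5% |

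The either-direction rate runs from about 10% to 23% against a nominal 5%. The rate in favour of LightBEAM runs from about 5% to 12% against a nominal 2.5%. Adding the composite as a sixth test, modelled as the mean of the four symptom scales, gives 18.4% at ρ = 0.5, hardly more than the five scales alone.

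**The case against.** The strongest reply is that Aim 2 is the operational section, speaks of a composite primary score in the singular, and can be read as making it the one primary outcome. On that reading, with one contrast, the error rate is the nominal one. The reading is possible and the conditional figures must allow for it. It does not settle the matter: it leaves the primary status of parenting quality in the Objectives unexplained, sits badly with the plural that follows in Aim 2, and gives no score for randomized co-parents.

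A reader might infer from the composite sentence that efficacy will be judged by change within arms. The article does not support that. The Objectives compare with a waitlist, the next sentence of Aim 2 models treatment over time by condition, and the analysis-population section {27c} analyses by initial randomization. What stands is that the composite sentence is badly worded and that the wave is unnamed.

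A reader might also infer that the chance of a false claim of effectiveness is some fixed multiple of 5%. That is not supported either. Alpha, the number of tests, the correlation and an any-one-counts rule would all have to be supplied from outside the article. The two-sided rates also include rejections against LightBEAM; a false claim of benefit is about half as frequent and belongs beside 2.5%.

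Finally, the absence of a multiplicity procedure is not by itself a fault here. A condensed article may leave that to an analysis plan that is not shown. The point rests on the disagreement between two stated definitions.

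**Conclusion.** The point holds as an internal contradiction. The Objectives and Aim 2 name different primary outcomes, one including parenting quality and the other excluding it, and neither the deciding outcome nor the deciding wave is fixed. A between-arm model is stated, so the weakness is in what it is applied to and when.

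The possible effect on error is about 10% to 23% family-wise, roughly half of it favouring LightBEAM, but only if any one of 3 to 5 outcomes can count at two-sided 5% with correlation between 0 and 0.8. With the composite alone at one contrast, the inflation is nil. The article does not say which of these applies. This should be corrected, and the correction is small.

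**What to change.** Reconcile Objectives {10} and the Aim 2 text so that one contrast decides Aim 2. One workable form:

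- **Outcome and contrast:** the LightBEAM-minus-waitlist difference in change (arm-by-time term) in the individualized composite score, at a stated alpha.
- **Wave:** post-intervention/re-baselining, with six months supportive.
- **Population:** main participants, or all randomized participants if the composite is explicitly defined for co-parents.
- **Other scales:** PHQ-9, GAD-7, PROMIS Anger and PSI individually labelled secondary. If parenting quality is to stay primary, test the Parenting Scale second in a fixed sequence, only if the composite is significant; otherwise label it secondary too.
- **Wording:** in the composite sentence, replace change over time with the difference between conditions in change.

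Which outcome leads is the sponsor's choice; what matters is that both sections make the same one. The cost is wording in two sections, plus a definition for co-parents if they are kept in the primary analysis. No new data or participants are needed. The downside is that individual scales can no longer support stand-alone primary claims.

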### Trial design {12}

Using a two-arm clinical design, participants will be randomized in a 1:1 allocation to be placed in either the 12-week LightBEAM program or the waitlist control. After the 12-week LightBEAM program has been completed by the intervention condition, participants in the waitlist control group will have one month to complete the “re-baselining questionnaires and online orientation prior to gaining access to the LightBEAM intervention. Participants in the intervention condition will complete post-questionnaires at the same time that the waitlist control completes re-baselining questionnaires. Longitudinal self-report questionnaires will be administered digitally at three timepoints: pre-intervention, post-intervention, and at six months follow-up.

## Methods: participants, interventions and outcomes

### Study setting {13}

The study will take place in Canada across all ten provinces and three territories. The study coordination team will be located in the center of Canada, in Winnipeg, Manitoba. Participants will be Canadian primary caregivers of children (1.5–8 years old) who are experiencing elevated levels of anger, depression, anxiety, and/or parental stress. Participants will be able to participate in LightBEAM across a variety of settings (e.g., at home, in rural and remote communities, at work etc.) as long as they are able to access the internet.

### Participant identification, recruitment, and consent {20, 32a}

Participants will be recruited from across Canada using a variety of online social media posts (e.g. Instagram, Facebook), radio ads, and through local organizations (e.g., daycares, community centers etc.). Once recruited, participant informed consent will be obtained via REDCap on two separate occasions; prior to completing the eligibility screener and before becoming enrolled in the program (i.e. before completing pre-questionnaires). Participant Canadian residency will be verified through checking their IP addresses. Should we not be able to verify their residency through IP, we will require participants to upload a photo of their Canadian identification (e.g., driver’s license, passport) alongside a photo of themselves. This verification process is designed to ensure only Canadian residents are accessing the LightBEAM program. The study team has successfully used this form of identity verification across other iterations of BEAM.

During the main consent process, all eligible participants will be asked if they would like to invite a co-parent to complete the LightBEAM program alongside them. Here, we define co-parent as the child’s other parent, stepparent, or other primary caregivers (e.g., child’s grandparents, uncle, auntie, etc.). If the main parent wishes to invite a co-parent to the program, they will be asked to enter their co-parent's email address. The co-parent will then complete a main consent form. Once co-parents have consented, they will go through the same identity verification, randomization, and assessment procedures outlined below.

### Eligibility criteria {14a}

Eligible participants must (a) identify as a primary caregiver of any gender to an 18 -to 107-month-old child (e.g., 1.5 - 8 years of age), (b) reside in Canada with access to an internet connection, (c) be aged 18 years or older, (d) be able to understand/read/speak in English, (e) report mild emotional distress across at least one of the following metrics; depression (Patient Health Questionnaire- 9 ≥ 5), anxiety (Generalized Anxiety Disorders Questionnaire ≥ 5) anger (Patient Reported Outcomes Measurement Information System Anger ≥ 14), or parenting stress symptoms (Parenting Stress Index Fourth Edition ≥ 110), and (f) have access to an electronic device. On the screener questionnaire, participants will be asked to contact the study coordinator via email if they do not have access to an electronic device as we will be able to provide a limited number of devices to those who do not have access. Although many parenting programs are open to caregivers who are parenting children under the age of six, LightBEAM includes caregivers who are parenting children up to the age of eight. Such a wide and inclusive age range was intentional to address the many behavioral challenges and delayed diagnosis that children encounter later in childhood, while also considering inclusivity and general lack of programming for parents of children who are older. Participants will be excluded if they are (a) below the age of 18 years, (b) parenting a child outside the designated age range, (c) live outside Canada, (d) have participated in previous iterations of BEAM. Co-parents will be subjected to similar inclusion and exclusion criteria as the main participant, however they will not have to report mild emotional distress. As such to be eligible, co-parents must (a) reside in Canada with access to internet connection, (b) be aged 18 years or older (c) be able to understand, read, and speak English and have access to an electronic device.

### Participant timeline {18}

The LightBEAM program will use a rolling recruitment model whereby eligible participants will be randomized and gain access to the program on the first Monday of each month (e.g., all eligible participants who complete the screener questionnaire during the month of September will be randomized and gain access to the program on the first Monday in October). This rolling recruitment model will continue until the target sample size is reached. While participant timeline in the program will vary within this model, all participants will complete the aforementioned questionnaires in the same order regardless of program start date. Co-parents will engage in the same process described below as the main participant, with the exception that co-parents will not (a) complete the screener questionnaire or (b) complete the Child Behavioral Checklist.

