#### Online orientation session

All eligible participants who complete the informed consent procedure will be asked to attend a mandatory online orientation session (approximately 60 min) before gaining access to the LightBEAM program. Parent coaches, who are trained research personnel who previously completed a different iteration of BEAM, will lead the online orientation sessions. Coaches will help orient participants to the app, answer questions about the program, and monitor the closed group forum within the app. Participants will book this online orientation through Microsoft BOOKINGS where they will be able to select a time slot that works best for their schedule. Participants randomized to the LightBEAM program will attend this orientation session shortly after completing pre-program questionnaires. Participants randomized to the waitlist control condition will attend this orientation session after completing the re-baselining questionnaires.

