### Blinding

Study coordinators, participants, data analysts, and the principal investigator will not be blind to the condition of the participants. All randomization will be completed by the LightBEAM study coordinator using the automated REDCap randomization function. A randomization table will be created and uploaded into REDCap by a data analyst at the Canadian Centre for Health Care Innovation.

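### Randomisation follows screener completion on a fixed Monday, with no requirement that the pre-intervention questionnaires be finished first, so an unblinded participant may report baseline knowing the arm

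*Protocol article*

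**What the plan says.** Participant timeline {18} gives the rule: "eligible participants will be randomized and gain access to the program on the first Monday of each month". The example that follows, dated to October's first Monday, names eligibility and a completed screener as what qualifies a person: "all eligible participants who complete the screener questionnaire during the month of September will be randomized and gain access to the program".

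Participant identification, recruitment, and consent {20, 32a} places the second consent "before becoming enrolled in the program (i.e. before completing pre-questionnaires"). For co-parents it adds: "Once co-parents have consented, they will go through the same identity verification, randomization, and assessment procedures outlined below".

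Online orientation session describes a "mandatory online orientation session (approximately 60 min) before gaining access to the LightBEAM program". It then says: "Participants randomized to the LightBEAM program will attend this orientation session shortly after completing pre-program questionnaires". Waitlist participants attend only after re-baselining, and Trial design {12} likewise holds back their access until then.

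On blinding: "Study coordinators, participants, data analysts, and the principal investigator will not be blind to the condition of the participants". Trial design {12} makes the questionnaires self-report, and Aim 2 analyses change from the pre-intervention timepoint in everyone randomised.

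**The concern.** The pre-intervention score is the starting point of every change examined under Aim 2. Randomisation makes the arms comparable only on what was measured before allocation, or on what allocation cannot affect. A self-report given after the arm is known meets neither condition. Someone just told to wait about three months, and someone just given the app, may answer mood and parenting items differently. That difference would look like a baseline imbalance and would enter the change contrast. A larger sample does not remove it.

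The direction is not fixed. If disappointment raises waitlist symptom scores at baseline, or optimism lowers LightBEAM scores, the program's effect is understated. The opposite shift would overstate it.

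A lesser consequence is that someone randomised who never returns a baseline still belongs to the all-randomised analysis set. Such losses could differ by arm.

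**Working it through.** There is no stated figure to reproduce: the sample size of 200-500 rests on feasibility, without alpha, power or effect size.

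**1. Order of steps, section by section**

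| Section | What it fixes | What it leaves open |
|---|---|---|
| Participant timeline {18} | Eligible and screened in one month, then randomised and given access on the first Monday of the next | Whether baseline must be complete |
| Consent {20, 32a} | Second consent before the pre-questionnaires; for co-parents, consent, then verification, randomisation and assessment as listed | Whether baseline is part of the assessment that follows randomisation |
| Online orientation session | Pre-questionnaires before orientation, and orientation before access | Whether the pre-questionnaires precede randomisation |

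No section makes a completed baseline a condition of allocation.

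**2. Calendar.** Recruitment runs from March to December 2025 (Trial status; the exact start day is not given, so 1 March is assumed). Gap = first Monday of the next month minus screening date.

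| Screened in | Randomised | Days from last day of month | Days from first day of month |
|---|---|---|---|
| March | 7 Apr | 7 | 37 |
| April | 5 May | 5 | 34 |
| May | 2 Jun | 2 | 32 |
| June | 7 Jul | 7 | 36 |
| July | 4 Aug | 4 | 34 |
| August | 1 Sep | 1 | 31 |
| September | 6 Oct | 6 | 35 |
| October | 3 Nov | 3 | 33 |
| November | 1 Dec | 1 | 30 |
| December | 5 Jan 2026 | 5 | 35 |

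The range is 1 to 37 days. Someone screened on 31 August or 30 November has one day.

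**3. Which measures are exposed.** Table 1 marks 12 instruments at pre-intervention. Four of them (PHQ-9, GAD-7, PROMIS Anger, PSI) are also marked at eligibility, so main participants have a score from before allocation. The other 12 - 4 = 8 have none. They include the Parenting Scale, CBCL, sleep and self-compassion. Co-parents complete no screener, so none of their measures has an earlier score.

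**4. Same-day access.** The timing of orientation depends on the arm, and orientation must precede access. For LightBEAM participants to be randomised and given access on one Monday, a self-booked session would have to fit between the two events. For waitlist participants the statement cannot hold, because access comes only after the 12-week program and re-baselining.

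**5. Sensitivity (illustration only).** Let b be the differential baseline shift in SD units and ρ the pre-post correlation. Both are assumptions. For an unadjusted change contrast:

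- bias = b
- SE = √(2(1-ρ)) × √(2/n), with n per arm
- type I error = 1 - Φ(1.96 - b/SE) + Φ(-1.96 - b/SE)

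Example: n = 100, ρ = 0.5, b = 0.1 gives SE = 1 × 0.141 = 0.141 and b/SE = 0.707. Type I error is then 0.109. The 1:1 split of 200-500 gives 100 to 250 per arm.

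| b | n = 100, ρ = 0.5 / 0.7 | n = 250, ρ = 0.5 / 0.7 |
|---|---|---|
| 0.1 | 0.109 / 0.150 | 0.201 / 0.303 |
| 0.2 | 0.293 / 0.447 | 0.609 / 0.823 |
| 0.3 | 0.564 / 0.782 | 0.918 / 0.991 |

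If baseline entered as a covariate instead, with equal SDs, the bias would be about ρ × b. At b = 0.1 that is 0.05 to 0.07 SD, smaller but not zero.

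**The case against.** The strongest reply is that the documents nowhere say baseline follows allocation. The September sentence illustrates monthly cohorts and need not list every condition. The co-parent sentence is a list of nouns, and assessment there may mean all later timepoints. The orientation sentence identifies an arm and fits either order. If pre-questionnaires precede orientation, orientation precedes access, and access falls on the randomisation Monday, then baseline would come first. The article is condensed, and the order of forms may be set elsewhere.

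Much of this stands: the text permits a post-allocation baseline and does not prescribe it. The last inference is weak, however, because it relies on the same-day access statement, which other sections contradict. The article also goes beyond leaving the order unsaid. It fixes a trigger and a date that, followed as written, can put randomisation first.

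A second reply is that the primary composite is built from the four measures on which people screen in, all of which have earlier scores for main participants. That is correct and narrows the exposure. But the stated analysis starts from the pre-intervention timepoint, and Objectives {10} also lists parenting quality as primary. The Parenting Scale, presumably its measure, is not on the screener.

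A reader might also infer that people are randomised before main consent or before residency is checked. The documents do not support that. Residence ("reside in Canada with access to an internet connection") is an eligibility criterion, randomisation is limited to eligible people, main consent precedes enrolment, and the co-parent list puts consent and verification ahead of randomisation. What is missing is only an explicit link to randomisation for main participants. Nor do the documents allow a count of people who would be randomised without a baseline.

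**Conclusion.** The point holds as a weakness in the stated sequence. Randomisation is tied to eligibility, a screener and a date 1 to 37 days later, completed baseline is nowhere required, and participants know their arm. The plan therefore allows the reference measurement for Aim 2 to be affected by allocation.

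The bias in an unadjusted change contrast equals whatever differential shift results. The documents give no value for it, so the type I error figures show sensitivity and do not estimate what will happen. They assume a shift of 0.1 to 0.3 SD, a correlation of 0.5 to 0.7, and an analysis in which baseline is a free outcome timepoint, which the article does not specify.

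Exposure is smallest for main participants on PHQ-9, GAD-7, PSI and PROMIS Anger. It is greatest for the Parenting Scale, CBCL, sleep and self-compassion, and for co-parents. Separately, the same-day randomisation and access statement contradicts the orientation and waitlist sections and must be reconciled with them whatever is decided about baseline.

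**What to change.** State one order, identically in Participant timeline {18}, the consent section and Online orientation session, for main participants and co-parents: main consent, identity check, completed pre-intervention questionnaires (at least the primary outcome measures), randomisation, notice of arm, then orientation and access according to each arm's schedule. Reword the same-day access statement to agree.

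Enforce the order with a REDCap rule that blocks randomisation until the required forms are complete. Move anyone incomplete to the next month's Monday. Limiting the lock to the primary outcome measures avoids excluding people who leave a minor form unfinished.

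The cost is a wording change and a REDCap setting, with no added visits or staff. In the 2025 calendar successive first Mondays are 28 or 35 days apart, so a rolled participant starts about a month later. The gap from screening also lengthens: someone screened on 1 March and moved from 7 April to 5 May waits 37 + 28 = 65 days, while the PHQ-9 and GAD-7 screener covers only the past two weeks. That is a real drawback, but a baseline completed just before randomisation gives a fresh score, whereas one affected by knowledge of the arm cannot be recovered afterwards.
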